##### Analysis

Survey responses will be downloaded to an Excel/Sav file.

Survey 1 responses evaluating RLO content, functionality and usability will be analysed with descriptive statistics in the form of frequencies and percentages. The data will be categorised to highlight areas of function or content that require amending.Survey 2 responses examining the impact and usefulness of the RLO on caregivers will be analysed with frequency tables and descriptive statistics. Data from the closed questions will be analysed to examine the impact of the RLO on changing behaviours related to responsive feeding.Survey 3 responses from HCPs exploring the implementation of the RLO and infographic will be a mixture of quantitative and qualitative data. The quantitative data from the two Likert scale questions will be analysed with frequency tables and descriptive statistics. The qualitative data gathered from the open questions will be analysed using content analysis [34].

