##### Recruitment for Evaluation

We will conduct a preliminary evaluation of the functionality, acceptability and usability of the RLO. Caregivers, HCPs and support workers (who were not part of the RLO development) will be recruited for either a formative survey or one of two summative surveys. Potential participants will be emailed a link to the RLO, patient information sheet (PIS), informed consent form (ICF) and respective survey. Participants will be given up to two weeks to access and complete the surveys and will be able to work through the RLO as many times as they require during this two-week period.

Survey 1—Up to 20 caregivers, HCPs and support workers will be asked to review the prototype RLO for content and ease of use.

Survey 2—Up to 30 caregivers will be recruited via Small Steps Big Changes (https://www.smallstepsbigchanges.org.uk/) and public contributors.

Survey 3—Up to 30 HCPs and support workers will be recruited via contacts at the Institute of Health Visiting and the Royal College of Midwives and gatekeepers at local NHS trusts who will be asked to send the survey via email to HCPs and support workers.

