##### Method

In the first step of the formative evaluation, public contributors, content experts and members of the healthy weight/healthy nutrition group at the Institute of Health Visiting will be asked to evaluate the proposed content to ensure that it is accurate. The public contributors include caregivers from a diverse range of backgrounds who have made different feeding choices (breast and/or formula). The RLO specification will be amended following this evaluation, and the content will be uploaded to the media platform. The prototype will be evaluated by public contributors to ensure that it is fit for purpose by looking at the fit between the content and media.

Next, an initial analysis will be conducted after completing the RLO through three online, anonymous surveys evaluating the acceptability and usability of the RLO. Participants will view and engage with the RLO, which typically takes 15–20 min, although they can review sections as many times as they wish. The anticipated time for completion of each survey is no more than 20 min.

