*Survey 1* (formative) responses will explore the usability of the RLO content and functionality and will be completed by caregivers, HCPs and support workers. The questions have been adapted from a survey tool by Johnson et al. exploring the usability of an e-learning resource to improve the knowledge and confidence of teachers working with children born pre-term [35]. Survey 1 (see Appendix A Table A1 survey A1) will consist of 9 closed questions with responses of agree, neutral or disagree to questions such as “the CRIB-RLO resource held my interest”.*Survey 2* (summative) (see Appendix A Table A2 survey A2) will be completed by caregivers and will ascertain the impact of the RLO on caregivers in terms of changing behaviours related to responsive feeding. There will be 7 closed questions on a 3-point scale from agree, neutral and disagree, including questions such as “The CRIB-RLO resource has improved my confidence in knowing how to feed my baby” and “The CRIB-RLO resource has increased my motivation to actively look for and respond to my babies cues during feeding”.*Survey 3* (summative) (see Appendix A Table A3 survey A3) will be completed by HCPs working with caregivers of infants and will explore the implementation of the RLO and infographic in practice within the NHS and other organisations. The questions have been developed based on a the Theoretical Framework of Acceptability (TFA) developed by Sekhon et al. [36]. The TFA can be used to evaluate the prospective and retrospective acceptability of healthcare interventions by both intervention deliverers and intervention participants. Preliminary reliability testing on the Sekhon et al. TFA adapted for examining the implementation of a telephone-assisted coaching framework revealed three main factors. These are affective attitude and effectiveness (Cronbach’s alpha 0.9, coherence and understanding (0.77), perceived burden (0.85), and suggesting an appropriate level of internal consistency for each construct [37].

Survey 3 will include a mixture of eight open and two closed questions on the implementation of the RLO in practice. Open questions include those such as “Can you describe any additional effort you might need to employ to implement the CRIB-RLO/Infographic into practice?” and closed questions such as “how prepared are you to deliver the CRIB RLO to caregivers?” with a 5-point Likert scale ranging from not at all prepared to highly prepared.

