## Appendix A

**Table A1 healthcare-12-00029-t0A1:** Survey A1: Usability of the CRIB-RLO.

Part 1 The CRIB-RLO resource ^1^ *Please indicate the extent to which you Agree, are Neutral or Disagree, with the following statements*		
The CRIB-RLO resource held my interest.		
Agree	Neutral	Disagree
2. I enjoyed using the CRIB-RLO resource.		
Agree	Neutral	Disagree
3. I found the CRIB-RLO resource easy to use.		
Agree	Neutral	Disagree
4. The visual elements added to my understanding of the topic.		
Agree	Neutral	Disagree
5. The audio commentaries were engaging.		
Agree	Neutral	Disagree
6. The case studies were engaging.		
Agree	Neutral	Disagree
7. I would prefer to use the CRIB-RLO resource than read written information.		
Agree	Neutral	Disagree
8. It was clear from the learning objectives what was in each section.		
Agree	Neutral	Disagree
9. I would recommend the CRIB-RLO resource to other caregivers or healthcare professionals/support workers.		
Agree	Neutral	Disagree
10. If you Disagree with any of the above statements, please add your suggestions for improving this resource?		
Final Version 1.1, 04/07/2023, IRAS 326807, FMHS 238 0323		

^1^ Questions derived from a survey tool used by: Johnson, S.; Bamber, D.; Bountziouka, V.; Clayton, S.; Cragg, L.; Gilmore, C.; Griffiths, R.; Marlow, N.; Simms, V.; Wharrad, H.J. Improving developmental and educational support for children born preterm: Evaluation of an e-learning resource for education professionals. *BMJ Open*
**2019**, *9*, e029720. https://doi.org/10.1136/bmjopen-2019-029720 [35].

**Table A2 healthcare-12-00029-t0A2:** Survey A2: Impact on caregivers.

Part 1 You			
Please indicate if you are a caregiver or a member of the CRIB public contributors group?			
*Please tick the box*			
Caregiver			
Public contributor			
If you are a caregiver, do you have a child less than one year old?			
Yes			
No			
2. Were you involved in the development of the CRIB-RLO resource?			
Yes			
No			
3. If you would like a link to the final resource please provide your email address below			
Part 2 Your learning			
*Please indicate the extent to which you Agree, are Neutral or Disagree, with the following statements*			
The CRIB-RLO resource has improved my understanding of when my baby is hungry and when they are full.			
Agree	Neutral	Disagree	
2. I am more likely to feed my baby based on their cues or signs than other ways for example, other people’s advice.			
Agree	Neutral	Disagree	

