3. I am more likely to feed my baby based on their cues or signs than other ways such as instructions on baby food tins.			
Agree	Neutral	Disagree	
4. The CRIB-RLO resource has improved my confidence in knowing **how** to feed my baby.			
Agree	Neutral	Disagree	
5. The CRIB-RLO resource has improved my confidence in knowing **when** to feed my baby.			
Agree	Neutral	Disagree	
6. The CRIB-RLO resource has helped me understand when it might be more difficult to read my babies signs and cues.			
Agree	Neutral	Disagree	
7. The CRIB e-learning resource has increased my motivation to actively look for and respond to my babies cues during feeding.			
Agree	Neutral	Disagree	

**Table A3 healthcare-12-00029-t0A3:** Survey A3: HCPs implementation into NHS/other organisations.

Part 1 You					
1. Please indicate your main area of work?					
					*Please tick the box*
Health visitor					
Parent support worker					
Midwife					
Children’s Nurse					
Nursery Nurse					
Breastfeeding or lactation consultant					
Other, please state					
2. Please indicate your employing organisation?					
Nottinghamshire Healthcare NHS					
Nottingham City Care Social Enterprise					
United Hospitals Lincoln					
Local Authority					
Charity or NGO					
Higher Education					
Other, please state					
3. Were you involved in the development of the CRIB-RLO resource?					
Yes					
No					
4. If you would like a link to the final resource please provide your email address below					
Part 2 Please provide your views on the CRIB-RLO and the Infographic ^1^					
Please indicate how you feel about the CRIB-RLO and Infographic?					
2. Can you describe any additional effort **you** might need to employ to implement the CRIB-RLO/Infographic into practice?					
3. Is the CRIB-RLO/Infographic a good fit with your own values around how you give infant feeding advice? Please describe any areas where there is conflict.					
4. Do you understand the information contained in the CRIB-RLO/Infographic?					
5. Do you think the CRIB-RLO/Infographic work well together as a way of improving caregiver responsive feeding?					
6. What aspects of the process of providing infant feeding advice in your team/organisation might alter as a result of caregivers having access to the CRIB-RLO?					
7. On a scale of 1-5 how effective do you think the CRIB intervention will be in changing the way caregivers feed their infants?					

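### Survey 2 is meant to examine the RLO's impact on changing feeding behaviour, but its only two feeding items neither name the RLO nor compare with earlier practice, so existing practice can count as impact on them

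*Protocol article*

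**What the plan says.** The protocol article states the aim of Survey 2 twice in Section 2.3.4 (Phase 4). Under Method, the survey "will ascertain the impact of the RLO on caregivers in terms of changing behaviours related to responsive feeding". Under Analysis, "Data from the closed questions will be analysed to examine the impact of the RLO on changing behaviours related to responsive feeding", and the responses "will be analysed with frequency tables and descriptive statistics".

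The design of the survey is as follows:

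- **Respondents.** "Up to 30 caregivers will be recruited via Small Steps Big Changes" and public contributors (Recruitment for Evaluation).
- **Timing.** "an initial analysis will be conducted after completing the RLO through three online, anonymous surveys evaluating the acceptability and usability of the RLO" (Method). The response window is short: "Participants will be given up to two weeks to access and complete the surveys". No rating before use and no comparison group are described.
- **Items.** Seven closed items answered agree, neutral or disagree (Appendix A, Table A2, Part 2). Item 2 reads "I am more likely to feed my baby based on their cues or signs than other ways for example", and goes on to give other people's advice as the example. Item 3 reads "I am more likely to feed my baby based on their cues or signs than other ways such as instructions on baby food tins". The other five items name the resource.

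Elsewhere the article is more modest. The third objective in Section 1 is an initial evaluation of acceptability. Section 2.1 describes an exploratory survey approach without hypothesis testing. Section 4 leaves effectiveness on responsive feeding behaviours to a future randomised trial.

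**The concern.** To say anything about a change in behaviour caused by the RLO, an item has to refer to behaviour, to a change from before, and to the RLO as the reason. No item in Survey 2 does all three. The items that credit the resource are about knowledge, confidence and motivation. The items about feeding do not credit the resource and do not refer to an earlier state.

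The stated analysis is a frequency table. On items 2 and 3, an Agree from a caregiver who was already guided by cues looks the same as an Agree from one who changed because of the RLO. The table cannot tell them apart, and no later analysis can recover a baseline that was not collected. This is the only summative survey of caregivers. The Discussion says the initial evaluation will allow for the later trial, so the article should be clear about what these percentages mean.

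**Working it through.** The article gives no sample-size or power figure on this point to reproduce. The check is a classification of the items, followed by an illustration of scale.

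**Step 1: classify the seven items (Table A2, Part 2).**

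| Item | What is rated | Names the resource? | Concerns feeding practice? |
|---|---|---|---|
| 1 | Understanding | Yes | No |
| 2 | Cues versus other people's advice | No | Yes |
| 3 | Cues versus tin instructions | No | Yes |
| 4 | Confidence (how to feed) | Yes | No |
| 5 | Confidence (when to feed) | Yes | No |
| 6 | Understanding | Yes | No |
| 7 | Motivation | Yes | No |

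Five items name the resource, and none of those five measures feeding practice. Two items concern feeding practice, and neither names the resource. The overlap is 0 of 7.

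**Step 2: read the comparison in items 2 and 3.** In both, the words after *than* are *other ways*. Grammatically the contrast is between two guides to feeding at the time of answering, not between two times.

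**Step 3: illustrate the scale with zero RLO effect.** Let *p* be the share of respondents who already feed mainly by cues. The documents give no value, so *p* is an assumption and a range is shown. Take the full n = 30. Suppose that every such caregiver reads the item literally and ticks Agree, and that nobody else does. Then:

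- expected Agree count = 30 × *p*
- chance that a majority agrees = P(X ≥ 16), with X ~ Binomial(30, *p*)

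| Assumed *p* | Expected Agree | P(at least 16 of 30 agree) |
|---|---|---|
| 30% | 9 | 0.006 |
| 50% | 15 | 0.43 |
| 70% | 21 | 0.98 |
| 90% | 27 | about 1.00 |

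These are upper figures. If only some respondents read the item literally, the expected count of such answers is 30 × *p* multiplied by that share. It falls to zero if everyone takes *more likely* to mean more likely since using the RLO. The documents do not settle which reading respondents will take, and the answers would not reveal it.

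**Step 4: compare the aims within the article.** Objective 3 (Section 1) is about acceptability. The general description of the three surveys (Section 2.3.4, Method) is acceptability and usability. Section 4 assigns effectiveness on behaviour to a later randomised trial. The Survey 2 sentences under Method and Analysis go beyond all three.

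**The case against.** The strongest reply is that the article already limits what it will infer. It calls the evaluation preliminary and exploratory, plans no hypothesis test, and leaves effectiveness to a randomised trial. That stands, and it lowers the severity. It excuses the lack of a test and of a sample-size calculation. It does not make the items measure what the two Survey 2 sentences say they will examine.

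A second reply is that items 2 and 3 sit in a survey titled as impact on caregivers, under a heading about learning, directly after an item that names the RLO. Some respondents will read them as asking about change since the RLO. That also stands: existing practice can be counted as impact, but need not be in every answer.

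A third is that capability and motivation are what the COM-B model says an intervention must address to change behaviour, so the other five items fit the article's framework. They do, and they ask about change credited to the resource. They still do not measure behaviour.

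A reader might infer more than the documents support:

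- **That Survey 2 will be reported as proof of behaviour change, or as a headline result.** The article says examine and ascertain. It names no primary outcome, threshold or progression rule that depends on the Agree rate.
- **That all of Survey 2 is contaminated by existing practice.** The problem reaches two of the seven items.
- **That a paired before-and-after rating is required.** Asked twice in one sitting, it would give practice no time to change. Spread over the two weeks, it would need linkage of anonymous responses. Without a comparator it still would not attribute change to the RLO.
- **That confidence intervals are part of the remedy.** They concern precision, which is a separate matter.

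**Conclusion.** The point holds in a limited form. The Method and Analysis text gives Survey 2 an aim, impact on changing behaviours, that a single rating after use without baseline or comparator cannot meet. On items 2 and 3, existing practice can be counted as impact. The item classification follows directly from the printed survey and rests on no assumption. The size of any distortion is not known. The range of 9 to 27 Agree answers out of 30 with no RLO effect rests on assumed baseline shares of 30% to 90%, a literal reading by all respondents and the full 30 responses. No planned test, sample size or stated decision changes, so this should be fixed but does not undermine the study. It is best done before fielding, because items 2 and 3 cannot be repaired once answers are in.

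**What to change.** Two changes are enough.

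1. **Table A2, Part 2, items 2 and 3.** Anchor both to the RLO and to earlier practice. For example: *Since using the CRIB-RLO resource, I am more likely than before to go by my baby's cues rather than by other people's advice*, with the parallel wording for instructions on baby food tins.
2. **Section 2.3.4, Method and Analysis, Survey 2.** Replace the aim of impact on changing behaviours with perceived impact on understanding, confidence, motivation and intention. This brings both places into line with objective 3, with the general description of the surveys, and with the Discussion.

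The reworded items are still self-reports without a comparator, so the second change is needed as well as the first. The cost is a small amendment to the survey and a less ambitious claim. The frequency-table analysis and the number of respondents stay as they are.

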### 2.5. Data Storage

All data will be treated as confidential and stored according to the GDPR 2018, Data Protection Act 2018. Working data will be stored on the University of Nottingham’s provided storage Microsoft Teams to enable data to be shared within the research team. Research data will be stored on the University of Nottingham’s OneDrive.

## 3. Results

### Dissemination

The findings including a description of the final RLO will be written up and published in a peer-reviewed journal. The findings will be presented at academic conferences in the areas of infant feeding, health psychology and digital health, and to stakeholders such SSBC. Virtual knowledge exchange and dissemination events will be held virtually with HCPS, caregivers and charitable NHS representatives. The RLO for caregivers will be circulated via public contributors, social media and parenting organisations such as the NCT, who will be asked to provide a link to the RLO via their webpages. Professional bodies will be made aware of the RLO in order to direct HCPs/support workers to pass the RLO on to caregivers. The accompanying infographic for HCPs and support workers will be disseminated via professional networks including the Royal College of Midwives, the British Nutrition Foundation and the Institute of Health Visiting. Higher education institutions that train midwives and health visitors will be sent a link to the infographic. The RLO will be uploaded onto the HELMOpen repository (www.nottingham.ac.uk/helmopen, accessed on 1 October 2023) which provides free global access to RLOs and has registered more than 5 million users. The usage is tracked via Google Analytics, and optional feedback forms are routinely collected as measures of impact.

## 4. Discussion

Whilst population-based approaches are needed to address the multiple and complex causes of childhood obesity, individual prevention efforts that support parents with infant feeding make a useful contribution. There is strong evidence that individual obesity prevention interventions delivered during early life that promote and support responsive feeding result in healthier weight trajectories for infants [15]. However, there is no universal information and support focused on responsive feeding; thus, there is a need to improve information for caregivers who feed infants and the HCPs who work with them. This study will co-produce a RLO for caregivers of infants to increase awareness, understanding and use of responsive infant feeding behaviours. In addition, we will developed infographic guidance for HCPs and support workers to use with caregivers alongside the RLO.

This research will been conducted in a comprehensive, systematic and evidence-based way by applying the MRC framework for complex interventions [23], the COM-B model and the ASPIRE approach [29]. This will help to ensure that the developed RLO and infographic responsive feeding outputs are robust and acceptable to both caregivers of infants and the HCPs working with them.

The co-design and initial evaluation of the RLO and infographic will allow for future testing of the intervention effectiveness on both responsive feeding behaviours and child weight outcomes within a randomised control trial. Providing improved support for responsive feeding for caregivers and HCPs who work with them has the potential to reduce non-responsive feeding practices such as overfeeding, which can lead to obesity.

## Figures and Tables

**Figure 1 healthcare-12-00029-f001:**
[figure not shown]
Outline of study phases and components.

**Table 1 healthcare-12-00029-t001:** Potential RLO components, COM-B elements and TDF domains.

Topic Idea	COM-B Component	TDF Domain
How do I work with others to help me carry out responsive feeding?	Opportunity	Social influences
What can I change around me to improve my ability to responsive feed?	Capability	Behavioural regulation; Environment
What are the cues for hunger/fullness from my baby?	Capability	Knowledge/Skills
Why should I carry out responsive feeding?	Motivation	Goals/Intentions

## Data Availability

Data created and analysed in this study will inform the RLO development. Data sharing is not applicable to this article.

## Appendix A

**Table A1 healthcare-12-00029-t0A1:** Survey A1: Usability of the CRIB-RLO.

Part 1 The CRIB-RLO resource ^1^ *Please indicate the extent to which you Agree, are Neutral or Disagree, with the following statements*		
The CRIB-RLO resource held my interest.		
Agree	Neutral	Disagree
2. I enjoyed using the CRIB-RLO resource.		
Agree	Neutral	Disagree
3. I found the CRIB-RLO resource easy to use.		
Agree	Neutral	Disagree
4. The visual elements added to my understanding of the topic.		
Agree	Neutral	Disagree
5. The audio commentaries were engaging.		
Agree	Neutral	Disagree
6. The case studies were engaging.		
Agree	Neutral	Disagree
7. I would prefer to use the CRIB-RLO resource than read written information.		
Agree	Neutral	Disagree
8. It was clear from the learning objectives what was in each section.		
Agree	Neutral	Disagree
9. I would recommend the CRIB-RLO resource to other caregivers or healthcare professionals/support workers.		
Agree	Neutral	Disagree
10. If you Disagree with any of the above statements, please add your suggestions for improving this resource?		
Final Version 1.1, 04/07/2023, IRAS 326807, FMHS 238 0323		

^1^ Questions derived from a survey tool used by: Johnson, S.; Bamber, D.; Bountziouka, V.; Clayton, S.; Cragg, L.; Gilmore, C.; Griffiths, R.; Marlow, N.; Simms, V.; Wharrad, H.J. Improving developmental and educational support for children born preterm: Evaluation of an e-learning resource for education professionals. *BMJ Open*
**2019**, *9*, e029720. https://doi.org/10.1136/bmjopen-2019-029720 [35].

**Table A2 healthcare-12-00029-t0A2:** Survey A2: Impact on caregivers.

Part 1 You			
Please indicate if you are a caregiver or a member of the CRIB public contributors group?			
*Please tick the box*			
Caregiver			
Public contributor			
If you are a caregiver, do you have a child less than one year old?			
Yes			
No			
2. Were you involved in the development of the CRIB-RLO resource?			
Yes			
No			
3. If you would like a link to the final resource please provide your email address below			
Part 2 Your learning			
*Please indicate the extent to which you Agree, are Neutral or Disagree, with the following statements*			
The CRIB-RLO resource has improved my understanding of when my baby is hungry and when they are full.			
Agree	Neutral	Disagree	
2. I am more likely to feed my baby based on their cues or signs than other ways for example, other people’s advice.			
Agree	Neutral	Disagree	
3. I am more likely to feed my baby based on their cues or signs than other ways such as instructions on baby food tins.			
Agree	Neutral	Disagree	
4. The CRIB-RLO resource has improved my confidence in knowing **how** to feed my baby.			
Agree	Neutral	Disagree	
5. The CRIB-RLO resource has improved my confidence in knowing **when** to feed my baby.			
Agree	Neutral	Disagree	
6. The CRIB-RLO resource has helped me understand when it might be more difficult to read my babies signs and cues.			
Agree	Neutral	Disagree	
7. The CRIB e-learning resource has increased my motivation to actively look for and respond to my babies cues during feeding.			
Agree	Neutral	Disagree	

**Table A3 healthcare-12-00029-t0A3:** Survey A3: HCPs implementation into NHS/other organisations.

Part 1 You					
1. Please indicate your main area of work?					
					*Please tick the box*
Health visitor					
Parent support worker					
Midwife					
Children’s Nurse					
Nursery Nurse					
Breastfeeding or lactation consultant					
Other, please state					
2. Please indicate your employing organisation?					
Nottinghamshire Healthcare NHS					
Nottingham City Care Social Enterprise					
United Hospitals Lincoln					
Local Authority					
Charity or NGO					
Higher Education					
Other, please state					
3. Were you involved in the development of the CRIB-RLO resource?					
Yes					
No					
4. If you would like a link to the final resource please provide your email address below					
Part 2 Please provide your views on the CRIB-RLO and the Infographic ^1^					
Please indicate how you feel about the CRIB-RLO and Infographic?					
2. Can you describe any additional effort **you** might need to employ to implement the CRIB-RLO/Infographic into practice?					
3. Is the CRIB-RLO/Infographic a good fit with your own values around how you give infant feeding advice? Please describe any areas where there is conflict.					
4. Do you understand the information contained in the CRIB-RLO/Infographic?					
5. Do you think the CRIB-RLO/Infographic work well together as a way of improving caregiver responsive feeding?					
6. What aspects of the process of providing infant feeding advice in your team/organisation might alter as a result of caregivers having access to the CRIB-RLO?					
7. On a scale of 1-5 how effective do you think the CRIB intervention will be in changing the way caregivers feed their infants?					
1. Not effective at all	2. Slightly effective	3. Moderately effective	4. Very effective	5. Highly effective	
8. Please let us know why you have given this score?					
9. On a scale of 1-5 how prepared are you to deliver the CRIB intervention to caregivers?					
1. Not prepared at all	2. Slightly prepared	3. Moderately prepared	4. Very prepared	5. Highly prepared	
10. Is there any more training you need to help you prepare to deliver the CRIB-RLO?					

^1^ Questions based on a framework developed by: Sekhon, M.; Cartwright, M.; Francis, J.J. Acceptability of healthcare interventions: An overview of reviews and development of a theoretical framework. *BMC Health Serv. Res.*
**2017**, *17*, 88. https://doi.org/10.1186/s12913-017-2031-8 [36].

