## 2. Materials and Methods

### 2.1. Design

This is a mixed-method study involving qualitative co-design workshops with caregivers and HCPs/support workers and a combination of quantitative and qualitative approaches to inform RLO development and evaluation. A mixed-method design enables us to gather comprehensive information from both caregivers and HCPs beyond that which would be possible from a single quantitative or qualitative approach. In addition, the use of qualitative, interactive approaches enables more in-depth and rich data which are complemented by the broader reach of data captured via the survey approaches used. This study does not involve quantitative hypothesis testing and instead involves an exploratory survey approach where sample size calculations have not been conducted. This study will instead aim to recruit a broad representative sample of participants to address the research aim.

The BCW framework [21] and the Behaviour Change Techniques Taxonomy (BCTT) [28] will be utilised to co-create a behaviour change RLO with caregivers, HCPs and support workers. The Am, **S**toryboarding, **P**opulate specification, **I**mplement media, **R**eview and release prototype, **E**valuate (ASPIRE) approach [29] for designing digital education resources will be used, including stakeholder involvement in co-designing the RLO and infographic for HCPs and support workers. As part of the final evaluation step, preliminary summative and formative evaluation of the usability, acceptability and implementation of the RLO and infographic will be undertaken.

Due to the lack of guidelines for the reporting of mixed-method research, the Consolidated Criteria for Reporting Qualitative Research (COREQ) checklist [30] will be followed in conducting and reporting this research.

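### Survey 1 should show what to amend, but it never asks whether the feeding information is clear or relevant, and requests suggestions only from those who disagree

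*Protocol article*

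**What the plan says.** Three places in section 2.3.4 of the protocol article set the purpose of Survey 1. Under Recruitment for Evaluation, up to 20 caregivers, healthcare professionals and support workers are "asked to review the prototype RLO for content and ease of use". Under Method, the "responses will explore the usability of the RLO content and functionality", and the survey "will consist of 9 closed questions with responses of agree, neutral or disagree". Under Analysis, answers are "analysed with descriptive statistics in the form of frequencies and percentages", and then "The data will be categorised to highlight areas of function or content that require amending".

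Appendix A, Table A1 prints the whole instrument and marks it as a final version. It has nine statements rated Agree, Neutral or Disagree, followed by one open item: "If you Disagree with any of the above statements, please add your suggestions for improving this resource".

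**The concern.** A formative survey earns its place by telling developers what to change. For that it needs items on the thing being judged, and a way for respondents to say what is wrong. Content is half of this survey's stated remit, yet no rated item takes up the clarity or relevance of the feeding information. The one item that can collect a reason or a suggestion is addressed only to people who reject a statement.

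All nine statements are worded favourably and the scale has three points, so a respondent with a mild reservation may choose Neutral and is then not asked to explain it. A respondent who likes the resource but was confused by one section can truthfully agree with everything and is not asked either. The survey could then return reassuring percentages with few suggestions, and unclear content could pass into the summative surveys and the released resource.

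**Working it through.** No sample-size or error-rate calculation applies. Section 2.1 describes an "exploratory survey approach where sample size calculations have not been conducted". The check is a count of items, a reading of what each one asks, and a labelled illustration.

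**Item count.** Table A1 has items 1 to 9 closed and item 10 open. This reproduces the nine closed questions stated under Method.

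**What the rated items cover.**

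- General liking or preference: interest (1), enjoyment (2), preference over written material (7), recommendation (9).
- Function: ease of use (3).
- Named components: whether the visuals helped understanding (4), whether the audio was engaging (5), whether the case studies were engaging (6), whether the learning objectives made the sections clear (8).
- Clarity or relevance of the feeding information itself: 0 of 9.

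Item 4 comes closest, but it asks what the visuals contributed. Item 8 is about signposting.

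**Who is asked for suggestions.** Of the three response categories, one (Disagree) leads to the request in item 10. Neutral and Agree do not.

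**Other surveys.** Survey 2 (Table A2), for caregivers, has seven closed impact items and no open comment item; its only free-text field is for an email address. Survey 3 (Table A3), for professionals, asks every respondent whether they understand the information and asks the reason for an effectiveness score. Within the three surveys, item 10 is therefore the only place where a caregiver is asked for written suggestions, and it is conditional.

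**Illustration, on assumed rates.** Suppose 20 respondents and, on every item, 5% Disagree and 30% Neutral. These rates are assumptions and do not come from the document. Disagreement with any one of the nine statements is enough for item 10 to apply, so the expected number asked depends on how the answers overlap.

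- Disagree only, the same people each time: 20 × 0.05 = 1.
- Disagree only, independent answers: 20 × (1 − 0.95^9) = 20 × 0.370 = 7.4.
- Disagree only, no overlap: 9 × 20 × 0.05 = 9.
- Neutral or Disagree, the same people each time: 20 × 0.35 = 7.
- Neutral or Disagree, independent answers: 20 × (1 − 0.65^9) = 20 × 0.979 = 19.6.

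As worded, item 10 would reach about 1 to 9 of 20 on these rates. Put to everyone, it reaches all 20.

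**The case against.** The strongest reply is that Survey 1 is not the only check on content. Caregivers and professionals choose content in workshops 3 and 4. Advisory committee members peer review the specification. Public contributors, content experts and an Institute of Health Visiting group then assess accuracy, the specification is amended, and public contributors assess how content and media fit together. This stands, and it limits the consequence. It does not remove the point: accuracy and fit differ from clarity to a new user, and the survey respondents are people who took no part in development.

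A second reply is that the rated items and the Neutral answers are informative. This also stands. A reader might infer that no item touches content, or that Neutral answers are useless. The document supports neither. Items 3, 4, 5, 6 and 8 each name a function or component, and nothing in the Analysis text excludes Neutral from the tabulation. A high Neutral share on item 5 would point to the audio. What is missing is the reason and the change needed.

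A reader might also infer that respondents who do not disagree are prevented from commenting. The document does not say that the text box is hidden from them; they are simply not asked. Nor should the number prompted be read from a single item (1 person on the assumed 5%), because disagreement with any of the nine statements is enough.

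Finally, the items are adapted from an existing tool that is not at hand, so some choices may be deliberate. That is a reason to add to the form rather than replace items in it.

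**Conclusion.** The point holds as a minor, inexpensive improvement. Survey 1 is given the task of finding content to amend, but 0 of its 9 rated items ask whether the feeding information is clear or relevant, and its only request for suggestions is addressed to 1 of 3 response categories. Neutral answers can show where a named component is weak but not why.

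The counts come directly from the printed instrument and need no assumption. How many useful suggestions would be lost is unknown: the range of 1 to 9 of 20 asked rests on assumed rates, and the document gives no basis for predicting how often mild dissatisfaction would be recorded as Neutral. There is no contradiction, wrong figure or biased estimate here. Treating every Neutral answer as a defect would go too far, since indifference is not a fault.

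**What to change.** - Put item 10 to all respondents, for example: *Which section or feature, if any, was unclear, not relevant to you or did not work well, and what should change?*
- Add one rated item, for example: *The information was clear and relevant to me.*
- Keep the existing nine items and the planned tabulation.

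The cost is one reworded and one added question for at most 20 respondents, slightly more free text to read, a small departure from the source survey, and an update to a form already marked final. The stated count of nine closed questions would become ten; no existing figure needs correcting.
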